##### Power and sample size

Meta-analysis of studies of cognitive impact in healthy older adults suggest Cohen’s d within groups was 0.325 for aerobic exercise and 0.327 for cognitive training [18]. A power analysis in Gpower assuming two independent means indicated 118 people per arm are necessary to have 80% power to detect this magnitude of a difference between samples. Due to the group-randomized nature of the current trial, it is possible that a higher n is required. The scope of this pilot funding opportunity limits us to just 25 aMCI patients and their 25 partners per arm, leading to a total of 75 aMCI patients and their 75 partners. The results of the current trial may serve as pilot data for future studies.

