### Randomization and blinding

The group nature of intervention allows participants to compare their experiences, so individualized randomization poses a risk for diffusion of treatment effects. However, the group format limits in the ability to randomize per couple. Thus, we will block randomize by group instead of by participant assuring equal randomization of sessions to each of the three arms of the trial at each site. In other words, everyone in the first intervention period will receive the same treatment determined at random. The next intervention group will receive one of the two remaining arms also determined at random. The study biostatistician will randomize using a computerized random number generator to determine initial and second sessions at each site. The biostatistician is not involved in recruitment, assessment, or intervention delivery in any way. Due to the nature of the intervention, participants cannot be blinded. However, to mitigate selection bias, patients as well as study staff will be kept blind until recruitment for each session has been completed. Sessions will be offered sequentially three times in year 1 and include 6–12 individuals with aMCI and study partner couples per session. Hence, there will be the opportunity to block randomize nine (three sites × 3) sessions involving approximately 25 couples per arm for a total of 75 participants. A flow chart diagram showing summary of the pilot trial design can be found in Fig. 1.

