### Statistical methods

The primary analyses will use linear mixed effects models to examine change from baseline to post intervention (~ 6 months) in each of the outcomes. These models control for within-subject effects through the use of per-subject random effects for slopes and intercepts over the six-month follow-up period. We will estimate the degree of change over time in each of the specific measurement intervals within randomized groups and test for differences in these changes between groups while conforming to linear model assumptions. We will evaluate the assumptions required for the appropriate use of linear models and will apply any needed transformations in the data to conform to the model assumptions. Analyses will be conducted to assess the aims listed above. In addition, to make it possible to identify which individuals are most likely to benefit from the interventions, we will incorporate variables to evaluate whether variables either attenuate or modify cognitive or imaging changes. Additional analyses are currently unknown. Missing data will be handled based on what appears to be most appropriate for the analysis being conducted. No interim analyses will be conducted.

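### Nine sessions are randomised, but the primary model names only per-subject random effects, so the between-arm tests do not match the unit of randomisation

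*Protocol article*

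**What the plan says.** Under Randomization and blinding, the allocation unit is the group: "Thus, we will block randomize by group instead of by participant". All members of a session share one arm, since "everyone in the first intervention period will receive the same treatment determined at random". The count is explicit: "there will be the opportunity to block randomize nine (three sites × 3) sessions involving approximately 25 couples per arm". Each site therefore runs each arm once. Session size is also given: sessions "include 6–12 individuals with aMCI and study partner couples per session".

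Under Statistical methods, the primary analysis is a linear mixed model of change from baseline to about six months. Its random part is described thus: "These models control for within-subject effects through the use of per-subject random effects", meaning subject intercepts and slopes. The same paragraph plans tests of differences in change between arms. It names no session effect, site factor, cluster-robust variance or small-sample degrees of freedom.

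The Aim 2 power section does recognise the design: "Due to the group-randomized nature of the current trial, it is possible that a higher n is required". It gives no ICC and no design effect.

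**The concern.** Arm varies only between sessions, so the error for an arm contrast must include variation between sessions given the same treatment. A model with subject effects alone takes its error from variation between people. If people in one session change more alike than people in different sessions at the same site, that error is too small.

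Some similarity is plausible on the article's own account. It avoids individual randomisation because "The group nature of intervention allows participants to compare their experiences", and the ten-day programme with its support groups is delivered to the session as a whole.

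Aims 1A and 2 are to estimate effect sizes, and the article says the results may inform larger studies. Overstated precision would pass into that planning. A model without a session level would also yield no estimate of the clustering that the next group-randomised trial has to allow for.

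**Working it through.** **The plan's own figure.** The Aim 2 section gives 118 per arm at d = 0.325 and 80% power for two independent means. n = 2(1.645 + 0.842)²/0.325² = 117.1, so 118. This reproduces with a one-sided 5% test (a two-sided test gives 149) and contains no allowance for clustering. Sidedness is a separate matter.

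**Inputs from the article.** 3 sites × 3 sessions = 9 sessions, 3 per arm; about 25 people with aMCI per arm; mean session size m = 25/3 = 8.33.

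**Assumed, because the article gives no value.** The ICC of six-month change within session, here 0.01, 0.05 and 0.10; and s, the share of that clustering due to site rather than to sessions within site.

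**Variance of an arm difference.** Set the total variance of change to 1. Site effects cancel because every arm runs once at every site, leaving

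Var = 2[(1 − s)·ICC/3 + (1 − ICC)/25].

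An analysis that ignores sessions uses about 2/25. The ratio of true to assumed variance is therefore

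R = 8.33(1 − s)·ICC + 1 − ICC.

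With s = 0 this is the usual design effect, 1 + (8.33 − 1)·ICC. R exceeds 1 when 1 − s > 3/25, that is, when more than about 12% of the clustering lies within site.

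| ICC | R, s = 0 (SE ratio) | R, s = 0.5 (SE ratio) | R, s = 1 (SE ratio) |
|---|---|---|---|
| 0.01 | 1.07 (1.04) | 1.03 (1.02) | 0.99 (0.99) |
| 0.05 | 1.37 (1.17) | 1.16 (1.08) | 0.95 (0.97) |
| 0.10 | 1.73 (1.32) | 1.32 (1.15) | 0.90 (0.95) |

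**Simulated type I error.** Change scores with no true effect, sessions of 8, 8 and 9 per arm, 40,000 replicates, nominal two-sided 5%. With two time points, a subject-level analysis is in effect an analysis of change scores.

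| ICC | Pairwise, s = 0 | Three-arm F, s = 0 | Pairwise, s = 0.5 | Pairwise, s = 1 |
|---|---|---|---|---|
| 0.01 | 5.8% | 6.2% | 5.6% | 4.8% |
| 0.05 | 9.4% | 11.3% | 6.9% | 4.6% |
| 0.10 | 13.6% | 18.3% | 9.2% | 4.3% |

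At ICC 0 the error is 5.0%. An analysis of the nine session means with arm and site as factors (9 − 1 − 2 − 2 = 4 df) held about 5% in every scenario.

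**Precision.** The 95% half-width for a standardised arm difference, treating people as independent, is 2.01 × √(2/25) = 0.57. With session-level error and s = 0, at ICC 0.01 / 0.05 / 0.10:
- 6 df (t = 2.45): 0.72 / 0.81 / 0.91
- 4 df with site as block (t = 2.78): 0.81 / 0.92 / 1.03

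Much of the widening comes from the degrees of freedom. At ICC 0 the half-width is already 2.45 × √(2/25) = 0.69 on 6 df.

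**The case against.** The strongest reply is that the paragraph is condensed. It lists no fixed effects, does not say that subject effects are the only random terms, and a fuller analysis plan may add session and site. This has some force: the article names no session term, but it does not rule one out. It does, however, go beyond saying that mixed models will be used. It states the random-effects structure and what that structure is meant to control, and leaves out the level at which treatment was assigned.

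A second reply concerns size and direction. A reader might infer that standard errors and p-values are bound to be too small, or that sharing a site adds to the inflation. The documents support neither. Every site runs every arm, so site similarity cancels from the arm contrasts, and ignoring it is mildly conservative. At ICC 0.01 the standard error is understated by only about 4% even in the worst case.

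Third, the shared exposure is limited. Daily group delivery lasts ten weekdays. In the following 24 weeks only yoga is described with a weekly session; cognitive training is tracked through a portal and wellness participants submit their own logs. The article does not say that each session has its own instructor. ICCs of 0.05 to 0.10 are therefore assumptions.

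Finally, this is a pilot that also aims at recruitment and retention rates, and leaving out a session term does not in itself bias the effect-size point estimates. That stands. It limits the harm to intervals, tests and the planning based on them.

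**Conclusion.** The point holds conditionally. The stated analysis does not match the unit of randomisation, and between-arm tests are planned from it. If sessions within a site differ in six-month change, those tests reject too often: about 6% / 9% / 14% pairwise at assumed ICC 0.01 / 0.05 / 0.10 when all session variance is within site, and about 6% / 7% / 9% when half is due to site. With no clustering the error is nominal; with clustering due only to site it is between 4% and 5%. These figures rest on assumed ICCs, sessions of eight or nine people and normally distributed change scores. The mismatch itself needs no assumption, so the analysis should be corrected whatever the ICC proves to be.

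**What to change.** State that arm comparisons are made at session level. The simplest form analyses the nine session-mean changes, adjusted for baseline where possible, with arm and site as fixed factors and 4 residual degrees of freedom. An equivalent is a model of individual change with a session random effect, site as a fixed block and session-level degrees of freedom (for example Kenward-Roger). Keep the session level whatever its variance estimate.

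Do not add session and session-by-time random effects on top of subject intercepts and slopes. With two time points the subject slope variance already cannot be separated from residual error, and there is only one session per site-by-arm cell.

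Report the ICC for each outcome with its interval, noting that nine sessions estimate it imprecisely and that it cannot be separated from site-by-arm interaction.

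The cost is a change of wording in Statistical methods, with no new data. The downside is wider intervals, which reflect the real precision of three randomised units per arm.

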#### Cognitive functioning

The Dementia Ratings Scale-2 (DRS-2) [22] will be used at baseline to asses overall level of cognitive functioning and after the six-month intervention period to monitor cognition during the six-month intervention period in the persons with aMCI. The DRS-2 assesses multiple cognitive domains and helps to distinguish individuals with aMCI from patients with Alzheimer’s dementia and healthy controls [23].The CogState, a computerized cognitive assessment, will be used to monitor more specific cognitive domains at baseline and after the six-month intervention period in the person with aMCI. CogState is sensitive to cognitive aging effects in MCI and dementia and therefore to interventions that remediate these effects [24]. The following subtasks of the CogState will be used: Detection task – a simple reaction time paradigm that measures psychomotor function; Identification task – a choice reaction time paradigm that measures visual attention; One Card Learning task – a continuous visual recognition learning task that assesses visual recognition memory and attention; One Back task – a task that assesses working memory and attention.The Rey Auditory Verbal Learning Test (RAVLT) [25, 26] will be administered to assess declarative memory. A 15-word list will be read to the participants, after which they will be asked to repeat all words they remember. This will be done five times. After 30 min, a delayed recall and recognition trial will be conducted.The Word Stem Completion Test (WSCT) [27] will be administered to assess priming memory. A word completion method similar to the method used in previous studies [28, 29] will be used.The Mirror-Tracing Task (MTT) [30] will be used to asses procedural memory. Participants are asked to trace the cutout outline of a five-point star without touching the edges of the star while looking in a mirror. Their direct view of their own hand and the figure to be traced will be blocked. Testing consists of two blocks of five trials, separated by an interval of 15 min.The Serial Reaction Time Task (SRTT) will be administered as a procedural memory task that involves only a limited motor component. The SRTT was developed largely based on the SRTT used in previous research [31] and will be administered on an Android-run tablet (Samsung SM-T580NZWAXAR 10.1 Galaxy Tab A T580) using OpenSesame Software [32].At baseline, the Wide Range Achievement Test 4 (WRAT4) [33] reading subtest will be administered to assess the patients’ reading achievement and cognitive reserve. Participants read aloud a list of 55 words that increase in complexity throughout the task and 1 point is awarded for each correctly pronounced word. Previous studies have successfully utilized reading ability as a measure of cognitive reserve [34].

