
#### Functional status

All measures of functional status will be conducted at baseline and after the six-month intervention period.The study partners will be asked to fill out the Everyday Cognition (E-Cog) [35] about the individuals with aMCI’s functioning in instrumental activities of daily living (IADLs). The E-Cog is an informant-based measure that assesses the participant’s ability to perform everyday tasks in the following areas: memory; language; visuospatial abilities; planning; organization; and divided attention.The study partners will be asked to fill out the Functional Assessment Questionnaire (FAQ) [36] about the person with aMCI’s functional status. The FAQ is the standard functional measure required for use throughout the Alzheimer’s Disease Research Center network.The study partners will be asked to fill out the Treatment Diffusion Log about the person with aMCI’s and their own time spent on any type of physical exercise, computerized cognitive training, wellness behaviors, use of a calendar, and supportive therapy. This will be done to assess specific skills targeted by the interventions.The Memory Compensation Training Therapists will fill out the MCT Adherence Questionnaire about the person with MCI’s use of the calendar. This questionnaire assesses how well an individual utilizes the sections of the MCT calendar system. The evaluator will examine MCT compliance for two randomly selected days from the prior week. This will be done on the first day of treatment, as well as during the booster session.The Memory Compensation Training Therapists will also be asked to determine the MCT Training Score on the final day of the program This 0–6 score reflects the individual with MCI’s progress in the three phases of calendar training. A score of 0 reflects no progress while a score of 6 reflects mastery of all three training phases. Intermediate scores (1–5) reflect intermediate levels of training progress.The Short Physical Performance Battery (SPPB) [37] will be administered to the individuals with aMCI to monitor their physical performance. This includes a timed 8-ft walk, standing side by side, semi-tandem and full-tandem stance, and a timed arms-folded rise from seated to standing.

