#### Quality of life, mood, and anxiety

The quality of life, mood, and anxiety measures will be conducted at baseline and after the six-month intervention period.Both the persons with aMCI and the study partners will be asked to complete the Quality of Life-AD (AD-QOL) [38] at baseline and after six months. The AD-QOL is a 13-item measure developed for individuals with dementia that has been utilized in aMCI and with study partners. Individuals with aMCI and study partners rate their relationships, concerns about finances, physical condition, mood, energy level, memory, aspects of daily functioning, and overall life quality on a four-point scale.Both individuals with aMCI and study partners will be asked to complete the Center for Epidemiologic Studies Depression Scale (CES-D), a well validated 20-item self-report measure of depressive symptoms with a four-factor structure consisting of negative affect, lack of positive affect, somatic symptoms, and interpersonal difficulties subscales [39].Both the persons with aMCI and the study partners will complete the REACH Anxiety Inventory Form (REACH-AIF) [40], a 10-item rating scale modified from the State-Trait Anxiety Inventory, by the Resources for Enhancing Alzheimer’s Caregiver Health (REACH) project [41].

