#### MRI acquisitions

All images will be acquired using a 3-T MRI scanner (Siemens Prisma) that is controlled for quality and are monitored weekly. We will use imaging to assess the efficacy and to elucidate the mechanisms of intervention impact by measuring brain changes over the intervention period. The primary imaging outcomes will be structural MRI (sMRI), arterial spin labeling (ASL), and resting state fMRI. Diffusion tensor imaging (DTI) will also be acquired. In addition, we will also ascertain the degree of vascular pathology using fluid-attenuated inversion recovery (FLAIR) and susceptibility-weighted MRI. The detailed imaging protocol and imaging measures are described in the supplementary neuroimaging protocol, which can be found in Additional file 1.

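### For outcomes measured only at baseline and six months, the random-intercept-plus-random-slope model has more variance parameters than the data can identify

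*Protocol article*

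**What the plan says.** The Statistical methods section of the Protocol article names the primary analysis as "linear mixed effects models to examine change from baseline to post intervention (~ 6 months) in each of the outcomes", with "per-subject random effects for slopes and intercepts over the six-month follow-up period". It states no structure for the random-effects covariance, no fallback model and no baseline covariate.

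The outcome sections give the timing:

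- **DRS-2:** at baseline and "after the six-month intervention period to monitor cognition during the six-month intervention period in the persons with aMCI".
- **CogState:** "will be used to monitor more specific cognitive domains at baseline and after the six-month intervention period".
- **Functional status:** "All measures of functional status will be conducted at baseline and after the six-month intervention period". The same section places the memory compensation training measures at other times (first day of treatment, final program day, booster session), so the statement covers most of these measures, not all.
- **Quality of life, mood and anxiety:** "The quality of life, mood, and anxiety measures will be conducted at baseline and after the six-month intervention period".

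For imaging, the MRI acquisitions section speaks only of "measuring brain changes over the intervention period". The visible text gives no number of scans. It also gives no number of assessments for the RAVLT, the word stem, mirror-tracing and serial reaction time tasks, or the self-efficacy scales.

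**The concern.** A random slope describes how far individuals' trajectories differ from each other beyond measurement error. With two observations per person, a straight line passes through both points exactly, so nothing is left over to separate slope variation from residual error. At full enrolment there would be 75 × 2 = 150 observations of each such outcome and 75 × 2 = 150 random effects.

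Three things are at stake. First, some software will refuse the stated model or flag it as singular, and the section does not say what replaces it. Second, the trial is meant to supply pilot data for a larger study, and slope or residual variances taken from this fit would be artefacts. Third, Aim 1B relates changes in imaging to changes in cognition, function and mood. If predicted subject-level slopes were used for that, their values would depend on an arbitrary split.

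**Working it through.** **Inputs.** The model and the two occasions come from the sections quoted above; 25 participants with aMCI per arm (75 in total) comes from the Aim 2 sample-size text. The protocol gives no variances or correlations, so all variance values below are assumed for illustration. It also has no figure of its own on this point to reproduce; its 118 per arm does not enter.

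**1. Count parameters and moments.** Code the visits 0 and 1. Let A be the intercept variance, B the intercept-slope covariance, C the slope variance and R the residual variance. Then:

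- Var(y0) = A + R
- Cov(y0, y1) = A + B
- Var(y1) = A + 2B + C + R

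That is four unknowns in three equations. Moving (A, B, C, R) along (−1, +1, −2, +1) leaves all three unchanged.

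**2. Example.** All three rows give variances 1.0 and 1.1 and covariance 0.7:

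| A | B | C | R | Var(y0) | Cov | Var(y1) | AC − B² |
|---|---|---|---|---|---|---|---|
| 0.70 | 0 | 0.10 | 0.30 | 1.0 | 0.7 | 0.70 + 0 + 0.10 + 0.30 = 1.1 | 0.0700 |
| 0.85 | −0.15 | 0.40 | 0.15 | 1.0 | 0.7 | 0.85 − 0.30 + 0.40 + 0.15 = 1.1 | 0.3175 |
| 0.95 | −0.25 | 0.60 | 0.05 | 1.0 | 0.7 | 0.95 − 0.50 + 0.60 + 0.05 = 1.1 | 0.5075 |

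The last column is positive throughout, so each row is a valid random-effects matrix.

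**3. Likelihood.** The Fisher information for 75 participants with two common visits has rank 3 of 4. In one simulated data set (3 arms × 25, two visits), the log-likelihood was −176.897548 at each of the residual variances 0.02, 0.05, 0.10, 0.15 and 0.20. The matching slope variances ran from 0.551 down to 0.191.

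**4. What survives.** Var(y1 − y0) = C + 2R, which is 0.70 in every row of step 2. Only that sum matters for the contrast. In the simulated data the fitted variances and covariance were 0.7261, 0.8886 and 0.5116. The change variance is 0.7261 + 0.8886 − 2 × 0.5116 = 0.5915, and the standard error of an arm difference is √(2 × 0.5915 / 25) = 0.2175 for every split.

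**5. What does not survive.** The share of change variance attributed to true slope differences is C / (C + 2R): 0.10/0.70 = 0.14, 0.40/0.70 = 0.57 and 0.60/0.70 = 0.86 for the three rows. Predicted individual slopes inherit this arbitrariness.

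**6. Possible escapes.**

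- *Covariance fixed at zero (not stated).* There are then three parameters for three moments, so the model is just identified, with C = Var(y1) − Var(y0). In 4,000 simulated trials of 75 with equal true variances and correlation 0.7, this estimate was negative in about 49%.
- *Spread of visit dates around six months.* With assumed A = 0.70, B = −0.05, C = 0.15, R = 0.30 and n = 75, the standard error of C is about 1.69, 0.77 and 0.43 for visit-time standard deviations of 1, 2 and 4 weeks. All far exceed 0.15.
- *A third common visit.* There are then six moments for four parameters, and the model is identified.

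**7. Baseline adjustment (a separate matter of efficiency).** With equal visit variances and correlation ρ, the contrast variance after baseline adjustment relative to change scores is (1 − ρ²) / [2(1 − ρ)] = (1 + ρ)/2. This is 0.75, 0.85 and 0.90 at assumed ρ = 0.5, 0.7 and 0.8. It is an individual-level ratio that ignores session clustering.

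**The case against.** The strongest reply is that the section aims at mean change within arms and differences in change between arms. These are fixed effects and stay estimable. In a separate check on one simulated complete data set, the model as written converged, and its arm-by-time estimates and standard errors (0.1995) matched those of a random-intercept model and of a plain change-score regression. Only the standard errors of the variance components were undefined. This stands. A reader might infer that the primary analysis cannot be run at all, or that its treatment estimate would be wrong; the documents support neither. Nor does removing the slope cost precision. Any gain in precision comes from baseline adjustment, which has nothing to do with identifiability.

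A reader might also infer that every outcome is measured twice. The text does not establish that. The schedule in Fig. 3 and the imaging protocol in Additional file 1 are not shown, and the Statistical methods section refers to measurement intervals in the plural. Two visits is therefore only an assumption for imaging (the Aim 1 outcome), the RAVLT, the priming and procedural memory tasks, and self-efficacy.

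The article also states no covariance structure, so independent intercepts and slopes are a possible reading. That version is just identified, but step 6 shows how fragile it is.

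Finally, this is a pilot, and a full analysis plan may hold detail that the article omits. That excuses silence, but the random slope is a stated choice for each outcome.

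**Conclusion.** The point holds for the DRS-2, CogState, most functional status measures and the quality of life, mood and anxiety scales. With two common occasions and an unrestricted covariance, four variance parameters face three moments, and the components cannot be told apart. In the example, the share of change variance credited to true slope differences can be anything from 14% to 86% with no change in fit. The practical consequences are a refused or singular fit with no named replacement, and arbitrary variance components or subject-level slopes if these are reported or carried into Aim 1B. The article does not say that they will be.

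The arm contrasts are not biased and their standard errors do not depend on the split, so severity is moderate. The identifiability result rests on the two-occasion schedule and on visits at essentially common times. The illustrative variances affect only the size of the examples.

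**What to change.** For outcomes assessed only at baseline and six months, remove the per-subject random slope and state one of these:

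- the six-month value regressed on arm, site and baseline value; or
- a longitudinal model with a common baseline mean across arms and an unstructured 2 × 2 covariance.

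Either should carry a random effect for the randomised session. Keep random slopes only for outcomes with three or more assessments, and list which outcomes those are.

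The cost is a few sentences in the Statistical methods section, with no extra data or visits. One caution: with nine sessions and fixed arm and site effects, the session variance rests on 9 − 1 − 2 − 2 = 4 degrees of freedom. The text should say in advance how a zero estimate and small-sample inference will be handled.
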